#### Statistical analyses

Estimation of intervention effects (H1, H2, and H3 of Sub-study 1) will be computed using a ‘per-protocol’ analysis [67]. All classes in the intervention group not adhering to the classification of ‘regular EOtC’ (an average of > 150 min of weekly EOtC over the school year) and all classes in control group practicing too high amount of EOtC (average of > 150 min of weekly EOtC over the school year) will be excluded. These analyses will be complemented with sensitivity analyses, following the principle of ‘intention-to-treat’ [67] which will include all schools in the analyses irrespective of their adherence to the intervention or control condition.

Linear mixed models (LMM) will be used to analyse how post-test scores varies as a function of whether the pupils were assigned to the intervention or the control group while taking into account pre-test scores, sex, age, and random effects of classes and schools. Please, see the H1 and H2 pre-registration for further information on the pre-processing steps and statistical modelling used for these data [51]. The base model used to assess H3 (effects on school motivation, wellbeing, and academic achievement) will include baseline as a covariate and school and class ID as random factor, and group allocation as the fixed effect of primary interest. Follow-up stepwise modelling will be used to investigate the contribution of previously shown confounders, i.e. primarily the number of weekly EOtC sessions [26], age, and sex [23, 68, 69], to the base models. All sub-studies will be reported following the CONSORT statements and flowchart [70].

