### Intervention

The intervention is based on the TEACHOUT intervention [49]. It is comprised of a two-day training course (13 h in total) on EOtC for teachers who afterwards implement EOtC in 1–2 weekly sessions, a total of at least five hours per week, for one schoolyear (in this study, August 2022 to June 2023, Month 4 to 14, see Fig. 4). The EOtC sessions in the schools are delivered by one or more of the teachers across different school subjects in various places and settings outside the school buildings.

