**Fig. 4 Fig4:**
[figure not shown]
The MOVEOUT study design

The course was structured to provide the teachers with knowledge and understanding of the theory and practice of EOtC. The course was taught by expert EOtC teachers and teacher education specialists and included theoretical lectures, supplemented by illustrative examples in workshops and videos, and plenum discussions on local implementation. The training course took place on the 28th and 29th of April 2022 (after randomisation, Month 0, see Table 1). The course was supplemented by two one-hour inspirational webinars during the first half of the school year (in this study, in September and November 2022, i.e., during Month 4 to 9, see Table 1).

Teachers in the control group received the two-day training course on EOtC in April 2023, close to the end of the intervention group implementation closeout; however, early enough for them to use the course content in their planning of the following school year. Also, they will receive the two one-hour inspirational webinars in the autumn 2023.

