### Randomisation

Randomisation was performed by PE and MB on 1st of April 2022 (Month 0, see Fig. 4), and was made public on YouTube (see Supplementary Information, Additional file 1). Immediately after, the enrolled schools and teachers were informed by e-mail about the result of the randomisation process.

To ensure a balanced representation of grade levels across the intervention and control groups, stratified block randomisation in a 1:1 ratio was used (i.e., schools with participating classes in grade 4–6 and schools with classes 7–10 were randomised block wise in RStudio using the ‘dplyr’ and ‘readxl’ packages).

Due to the type of the intervention, it was not possible to blind the participants to group allocation. However, allocation levels will be coded before analyses and the analysts will not be informed about the codes before the final analyses have been performed.

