### Sub-study 1: effects of EOtC

#### Design

Effects of EOtC will be measured in a between-subjects design. PA measurements pre- and post-intervention will be collected in two intervals each (Test A and B) to account for seasonal variations. Data collection of the first PA pre-intervention measure commenced before randomisation and continued until just before randomisation (Pre-test A, Month -2 to -1, see Table 1). The second PA pre-measure was collected after randomisation and before the implementation of the intervention (Pre-test B, Month -1 to 0). School motivation, wellbeing, and academic achievement were measured at pre-test B.

The first PA post-measure data collection will commence during the end of the school year (Post-test A, Month 10 to 11, see Table 1). The second PA post-measure data collection will be assessed immediately before finalisation of the intervention (Post-test B, Month 11 to 12, see Table 1). School motivation, wellbeing, and academic achievement will be measured at post-test B.

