### Evaluation of implementation

#### Design

Adherence to the intervention will be investigated in a repeated design with weekly monitoring of EOtC practised during the intervention in the intervention group and control group (Month 4 to Month 14, see Table 1). Quality of delivery, variations, facilitating and limiting contextual factors at school, local, and municipality level, and teachers’ acceptability of the intervention will be investigated through semi structured interviews [81] with intervention group teachers taking place in the second half of the implementation period (Month 10, see Table 1).

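### The per-protocol set averages EOtC over the whole school year, which by the month labels runs past the last post-test, so later EOtC can decide whether a borderline class is analysed

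*Protocol article*

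**What the plan says.** In the protocol article, Sub-study 1, Statistical analyses, the intervention effects for H1, H2 and H3 are estimated per-protocol, with intention-to-treat as a sensitivity analysis. Intervention classes stay in only if they reach "an average of > 150 min of weekly EOtC over the school year". Control classes above the same average are removed.

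The period averaged is stated:
- Intervention: "at least five hours per week, for one schoolyear (in this study, August 2022 to June 2023, Month 4 to 14".
- Evaluation of implementation, Design: "weekly monitoring of EOtC practised during the intervention in the intervention group and control group (Month 4 to Month 14".

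The outcomes are placed earlier (Sub-study 1, Design). Post-test A comes "during the end of the school year (Post-test A, Month 10 to 11, see Table 1", and Post-test B comes "immediately before finalisation of the intervention (Post-test B, Month 11 to 12, see Table 1". Motivation, wellbeing and academic achievement are measured only at Post-test B. Table 1 gives Post-test B at 11 months and close-out at 14 months, with EOtC and weekly monitoring continuing through close-out.

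The Intervention section adds that control teachers had their two-day course in April 2023, to help them plan the following school year. Nothing in the article stops the average at the post-test.

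**The concern.** A per-protocol rule should classify a class by the exposure that could have produced its outcome. Teaching delivered after the last measurement cannot do that, but under this rule it still counts. A class just below the cut at Post-test B can be brought in by later EOtC, and one just above it can be dropped for a quiet end of year. Selection after randomisation is then partly selection after the outcome, and it happens in the main analysis.

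The arms are also not treated alike in the tail. Control teachers are trained in April 2023, inside the averaging window. If that raised their EOtC in the remaining weeks, it would move control classes only towards exclusion.

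**Working it through.** **1. Calendar.** Randomisation took place "on 1st of April 2022 (Month 0, see Fig. 4". For training, the article says: "The training course took place on the 28th and 29th of April 2022 (after randomisation, Month 0, see Table 1". Month 0 is therefore April 2022. August 2022 as Month 4 and June 2023 as Month 14 give the same origin, so Month 12 is April 2023. Months 4 to 14 inclusive are 11 calendar months.

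**2. Share of the average that follows the outcome.**
- Post-test B in Month 12: Months 13 and 14 follow, 2/11 = 18%.
- Post-test B in Month 11: Months 12 to 14 follow, 3/11 = 27%.
- Post-test A in Month 11 at the latest: at least 3/11 follow.
- Post-test B truly at the end of the intervention: close to 0.

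Months are weighted equally, because holiday weeks are not given.

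**3. What it takes to cross the cut.** Let x be the weekly mean up to Post-test B and y the weekly mean afterwards. With a two-month tail, (9x + 2y)/11 = 150 gives y = (1650 − 9x)/2. With three months, y = (1650 − 8x)/3.

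| x (min/week) | y, 2 of 11 | y, 3 of 11 |
|---|---|---|
| 130 | 240 | 203.3 |
| 140 | 195 | 176.7 |
| 160 | 105 | 123.3 |
| 98.4 | 382.2 | 287.6 |

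With a two-month tail, a class at 140 counts as above the cut if it then exceeds 195, and one at 160 falls out at 105 or less. The last row is the earlier study's control-group level (1.64 h × 60 = 98.4 min; Evaluation of implementation, Outcome measures). A typical control class is far from being excluded.

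**4. How many classes.** The article gives no spread of EOtC between or within classes, so these figures are an illustration on assumed inputs: 27 classes per arm and monthly minutes equal to the class mean plus a normal deviation with SD 60, truncated at 0.
- Intervention arm, mean 200 to 300, between-class SD 60 to 100: 0.05 to 0.57 class changes status with a one-month tail, 0.07 to 0.86 with two months, 0.10 to 1.10 with three.
- Control arm, mean 98, SD 40 to 80, two-month tail: 0.74 to 0.84 class with no change after training, and 1.28 to 1.57 if EOtC rose by an assumed 60 min (1.23 to 1.50 of these newly excluded). A longer tail with the same rise would give more.

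**5. Scale for the effect estimate.** The plan's power figure is not in dispute and only sets the scale. With 30 schools, 51 classes, 867 pupils and ICCs of 0.046 and 0.035, SE = √[4(0.035/30 + 0.046/51 + 0.919/867)] = 0.1119. This gives 94.4 to 94.7% one-tailed power at d = 0.374, against the stated 95%. One class-plus-school SD is √(0.046 + 0.035) = 0.285. With about 25 classes per arm, one misassigned class that differs by that much moves its arm mean by 0.285/25 = 0.011 SD, and 0.0114/0.374 = 3% of the design effect.

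**The case against.** The strongest objection is that the tail may hardly exist. The article's own words put Post-test B at the end of the intervention. The labels are also loose elsewhere: "The second PA pre-measure was collected after randomisation and before the implementation of the intervention (Pre-test B, Month -1 to 0". Randomisation on 1 April 2022 is itself Month 0, so that label fits only if Pre-test B fell in April. The description alone would allow May or June 2022, and a post-test a year later would leave a tail of 0 to 1 month. This stands. A reader might infer that a two-month gap is established fact, but the documents support only a range from near zero to about three months. It does not clear the rule, because the labels in three sections and Table 1 agree on a gap. Either the labels or the description must be wrong.

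Second, the pre-registration may fix the window. That is possible for H1 and H2, for which the article cites it, but the article does not cite it for H3. The article also states the window rather than leaving it out.

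Third, the whole-year average has a rationale. The intervention is one school year, and 73 to 82% of the window precedes Post-test B even on the labels. A longer average is also less noisy. With intervention mean 200, SD 60 and a two-month tail, the whole-year average misplaces 1.81 of 27 classes relative to their underlying mean, and the truncated one 2.01. That is a real but small cost. The relevant standard, though, is the EOtC delivered before the outcome, not a class's long-run habit.

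Fourth, a reader might infer that the April 2023 training distorts the control arm. The documents do not show this: the course was meant for the next school year, and the 60-minute rise is an assumption.

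**Conclusion.** The point holds as a minor defect. As written, the per-protocol rule lets EOtC after the last outcome measurement help decide which classes enter the main analysis. On the month labels, up to about 2 to 3 of the 11 months averaged are affected. If the description of Post-test B is right and its label wrong, the tail is close to nothing.

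Only classes near 150 minutes can change. Under the assumed variability that is roughly 0 to 1.6 classes per arm, and an atypical one moves its arm mean by about 0.011 SD. The documents do not support reading this as a demonstrated bias in the treatment effect: its direction is not established, and the number of classes near the cut is not given. The intention-to-treat analysis is unaffected. The 150-minute cut itself is not questioned here.

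**What to change.** In both arms, compute each class's average weekly EOtC only over weeks up to and including its own last post-test: Post-test B, or Post-test A if B is missing. One class set then serves H1 to H3. Keep the 150-minute cut. State the calendar dates of Post-test B and resolve the conflict between its month label and its description. Record the change before allocation codes are opened, and report how many classes change status compared with the whole-year average. If the pre-registration already fixes the window, align the article with it.

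The cost is one line of text and one recalculated average per class from weekly data already being collected. The average becomes slightly shorter and noisier. The weeks between Post-test A and B, about a month, still count for outcomes measured at Post-test A, which is the price of a single class set. Power is barely touched: going from 51 to 50 classes raises the standard error from 0.1119 to 0.1126, about 0.6%.

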### Recruitment and participants

We aimed to recruit ~ 54 classes (~ 81 teachers) from 30 Danish general (non-special need) education elementary schools; on average 1.8 classes per school, 1–2 teachers and 21 pupils per class, with a total of 1.134 pupils aged 10–16 years (see Fig. 3). Pupils with noteworthy health problems, reported by their parents or legal guardian, teachers, or investigators will be excluded from the analyses.

Schools in municipalities with larger proportions of citizens with lower levels of education than the average for the region were strategically invited for enrolment in the study. Schools located in the Capital Region and Region Zealand were invited to begin with. Thereafter, schools in Region of Southern Denmark were invited, and finally invitations were distributed nationally via teacher networks. School classes were not allowed to be involved in other school development or research projects.

Recruitment and enrolment started around two years before the implementation of the intervention and continued until randomisation (month − 18 to 0, see Table 1). Teachers were recruited via both municipal school directors and direct contact to local school principals. Municipalities and schools were initially contacted via e-mail and non-responders were then contacted via telephone. Online information meetings were held with school principals and teachers. Participating teachers informed the parents and were provided with written material available in Danish and English, and supplementary video material introducing the study (see Supplementary Information, Additional files 1, 3, and 4). Parents were given a letter with additional information about the study’s rationales and background, and an analogue consent form. The recruitment process was supported by general information on the MOVEOUT study project website (www.moveoutstudy.dk) [57].

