#### Outcome measures

Monitoring of the intervention, namely the degree and the characteristics of the EOtC implementation, will be measured with a short self-report teacher questionnaire distributed weekly to teachers by SMS every Friday during the implementation period. In the previous TEACHOUT study, non-intended EOtC implementation in the control group was found to be 1.64 h a week [39]. The questionnaire assesses the amount, place, mode of transportation, and school subjects used during EOtC sessions. The questionnaire is based upon the existing and validated EOtC implementation monitoring tool from the TEACHOUT study [38, 39].

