## Discussion

EOtC holds promise for improved health and education if implemented regularly and extensively. The threshold, if there is one, for ‘how much’ EOtC is required for health and education gains is uncertain, but previous experience and findings point to five hours a week as a minimum. However, this current understanding of EOtC rests on findings from previous studies (e.g. [24, 27, 29]) with inherent risks of bias. The MOVEOUT study investigates the effects of the intervention developed and conducted in the TEACHOUT study [38] with updated and strengthened design and measures. The foremost strengths and limitations of the MOVEOUT study are discussed below.

The MOVEOUT study aims to reach more solid conclusions of the effects and mechanisms of EOtC using randomised group allocation, quantification of the pedagogical and didactical elements that are posited to carry effects, and extensive monitoring. The study will not only be able to confirm or disconfirm previous assertions relating to EOtC, but also contribute to a deeper understanding of the so-called active ingredients. Pending the findings, the combination of these data sources provides considerable prescriptive potential for practice and policy.

The use of randomisation will minimise any influences on effect measures of teachers’ having different initial interest in and abilities for EOtC. It can be expected that being randomised to do what you as a teacher have hoped for when signing up for the study, i.e., being assigned to the intervention group, may affect pupil outcomes positively. It may also be that the teachers ending in the control group may not refrain from using EOtC. Therefore, the collected weekly monitoring data about EOtC practise among all classes in the project is important data to include in the analysis.

The MOVEOUT study enables an effect evaluation of EOtC-induced PA behaviours by having pre-intervention measures of PA in order to adjust post-intervention PA for baseline PA. We further use two pre-intervention and measures and two post-intervention measures to account for impacts of seasonal changes in weather. Such a design is seldom applied in the studies investigating the influence of comparable interventions on PA [21, 83], and will provide a more valid analysis of the intervention effect that the previous study on the effects of EOtC on PA [23].

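### The main estimate for H1–H3 is per-protocol and excludes classes on post-randomisation EOtC in opposite directions by arm; the randomised comparison is kept only as a sensitivity analysis

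*Protocol article*

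**What the plan says.** In the protocol article, Sub-study 1, Statistical analyses, the ranking of the analyses is explicit: "Estimation of intervention effects (H1, H2, and H3 of Sub-study 1) will be computed using a ‘per-protocol’ analysis". An intervention class stays in only if its EOtC averaged more than 150 min a week over the school year. On the other side the plan excludes "all classes in control group practicing too high amount of EOtC", defined by an average above the same 150 min. The intention-to-treat analysis complements this as a sensitivity analysis, with all schools included "irrespective of their adherence to the intervention or control condition".

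Other places that bear on the point:

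- **Discussion, purpose of randomising:** "The use of randomisation will minimise any influences on effect measures of teachers" differing at the outset in how interested they are in EOtC and how able they are to deliver it. The same paragraph expects that control teachers may use EOtC anyway.
- **Evaluation of implementation, Outcome measures:** EOtC minutes come from a weekly teacher self-report during the school year. In the earlier study "non-intended EOtC implementation in the control group was found to be" 1.64 h a week.
- **Randomisation:** participants could not be blinded, and schools and teachers were told their allocation immediately.
- **Intervention:** EOtC for at least five hours a week. The Discussion adds that "previous experience and findings point to five hours a week as a minimum".

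**The concern.** How much EOtC a class receives over the year is decided after allocation, by teachers who know their arm. It plausibly reflects the same interest and ability that randomisation was meant to balance. The rule removes low-EOtC classes from the intervention arm and high-EOtC classes from the control arm, so the two exclusions do not cancel. If classes with keener teachers also differ in activity, motivation, wellbeing or achievement for other reasons, both exclusions push the estimate the same way.

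The lead result for all three efficacy hypotheses could then partly reflect which classes remained in the analysis. The estimate that keeps the benefit of randomisation would be reported second.

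**Working it through.** **1. The plan's design effect, as a yardstick.** Inputs from Sample size and Recruitment: 30 schools, 1.8 classes per school (54 classes), 17 analysable pupils per class, ICC 0.035 (school) and 0.046 (class), one-tailed 5%, 95% power.

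SE² = 4 × [0.035/30 + 0.046/54 + 0.919/(54 × 17)] = 4 × 0.003020 = 0.01208, so SE = 0.1099.

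Detectable effect = (t₀.₉₅,₂₈ + t₀.₉₅,₂₈) × SE = (1.701 + 1.701) × 0.1099 = 0.374. This matches the stated d = 0.374. With the expected 51 classes the SE is 0.1119, the detectable effect 0.381, and power at 0.374 is 94.7%.

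**2. How many classes the rule removes.** The control mean comes from the earlier study: 1.64 h × 60 = 98.4 min. The between-class SD is not given.

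| Assumed control SD (min) | Share of control classes above 150 min |
|---|---|
| 40 | 9.9% |
| 60 | 19.5% |
| 80 | 25.9% |
| 100 | 30.3% |

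For the illustration, assume control SD 80 and intervention mean 250 with SD 100, all normal. Controls kept: Φ((150 − 98.4)/80) = Φ(0.645) = 0.741. Intervention classes kept: Φ((250 − 150)/100) = Φ(1) = 0.841. With 25.5 classes per arm, 25.5 × (0.741 + 0.841) ≈ 40 of 51 remain.

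**3. Spurious effect when the true effect is zero.** Let ρ be the correlation between a class's minutes and the class-level part of its outcome, whose SD is √0.046 = 0.2145. Truncation moves mean minutes, in SD units, by:

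- controls: −φ(0.645)/Φ(0.645) = −0.4375
- intervention: +φ(1)/Φ(1) = +0.2876

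The gap is 0.725, so bias ≈ 0.725 × 0.2145 × ρ = 0.1555ρ. This gives 0.031, 0.047, 0.062 and 0.078 SD at ρ = 0.2, 0.3, 0.4 and 0.5, and zero at ρ = 0.

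**4. Simulated null trials.** These used 30 schools, 51 classes, 17 pupils per class, the plan's ICCs, an analysis of school means and a one-sided 5% test. The adjusted version adds the baseline school mean, with an assumed pre/post correlation of 0.6–0.8.

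| ρ | Per-protocol bias, unadjusted (SD) | Rejection, unadjusted | Per-protocol bias, baseline-adjusted (SD) |
|---|---|---|---|
| 0.2 | 0.03 | about 9% | 0.01–0.02 |
| 0.3 | about 0.05 | about 11% | 0.02–0.03 |
| 0.5 | 0.08 | 15–17% | 0.03–0.05 |

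Adjusted rejection is about 7–14%. Over all runs, adjusted and unadjusted, the range is about 7–17%. Intention-to-treat shows bias of about 0 and rejection of about 5%. The closed form in step 3 agrees with the unadjusted column.

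**5. Sensitivity to the inputs.** With better adherence (intervention 300, SD 80; control SD 40), adjusted bias falls to 0.01–0.02 SD and rejection to 6–8%. With harsher inputs (SD 120 in both arms, intervention mean 200–300, ρ of 0.3–0.7 with the whole cluster-level outcome), unadjusted bias is 0.06–0.22 SD.

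**6. Threshold beside intervention.** Five hours is 300 min, and the adherence cut is 150 min, 150/300 = half. A class averaging 160 min counts as adherent in the main analysis while falling well short of the described intervention. The article does not explain how the two figures relate.

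**The case against.** The strongest reply is that the trial asks an efficacy question, that an adherence-based estimate addresses it, and that the planned model adjusts for pre-test score, sex and age. Baseline adjustment does help: in the illustration it removes roughly a third to two thirds of the bias. It does so, however, under the favourable assumption that minutes relate only to an outcome level the baseline also reflects. It does not correct for keener teachers changing outcomes during the year. An efficacy aim explains the interest in adherers, but it does not make exclusion after randomisation unbiased.

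Several stronger readings are tempting, and the article does not support them:

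- **That the benefit of randomisation is lost.** It is demoted. An intention-to-treat analysis of all schools is planned.
- **That only the keenest and the least keen teachers remain.** Selection is partial. On the assumed SDs, about 70–90% of control classes stay.
- **That the simulated percentages are this plan's error rate.** The SDs, the intervention mean and the correlation are assumed, and the simulated test is simpler than the planned mixed model.
- **That the protocol criticises the earlier study for this same bias.** The limitations it lists in the Background are others, chiefly a single physical activity measurement. The Discussion mentions risks of bias in previous studies only in general terms.
- **That the 150-minute cut contradicts the five-hour intervention.** A minimum-adherence cut below the target is possible. Here it is unexplained.
- **That the intention-to-treat set is itself compromised by the health exclusion.** Recruitment and participants says: "Pupils with noteworthy health problems, reported by their parents or legal guardian, teachers, or investigators will be excluded from the analyses". It is silent on when such reports are made, and a condensed article may leave that to the full protocol. This is a request for clarification and not part of this point.

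**Conclusion.** The point holds. The article itself, not an unseen plan, ranks per-protocol first for H1–H3 and defines exclusions that depend on post-randomisation teacher behaviour in opposite directions by arm. The lead estimate is therefore not a comparison of randomised groups.

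The existence of the problem follows from the text; its size does not. Under the stated assumptions the spurious effect is about 0.03–0.08 SD unadjusted (0.03/0.374 = 8% to 0.08/0.374 = 21% of the design effect) and about 0.01–0.05 SD after baseline adjustment (3% to 13%). One-sided rejection under the null is about 7–17% instead of 5%. If class minutes are unrelated to class outcome level there is no bias, only fewer classes. The matter should be settled before analysis because it decides which result leads for every efficacy hypothesis.

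**What to change.** Name the planned intention-to-treat analysis, with all randomised schools and classes analysed as allocated, as the primary analysis for H1–H3. Keep the per-protocol analysis as supportive, report the classes excluded in each arm, and reconcile its 150-minute threshold with the five-hour definition of the intervention.

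Optionally, add a supportive complier estimate that uses allocation as an instrument for weekly EOtC minutes, which are monitored in both arms. It must state its assumption that allocation acts only through minutes. The Discussion puts that in doubt, since it expects that receiving the hoped-for allocation may itself improve pupil outcomes.

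Cost: the main change swaps the roles of two analyses already planned and needs no new data. The intention-to-treat estimate will be diluted by non-adherence in either arm, and the text should say so. The optional complier estimate would have a wider interval.
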